### Listserv

A project listserv will be established to link all intervention participants to facilitate exchange of coping strategies, pose questions, and share preferred educational resources or any other information relative to their everyday and disease-specific experiences and/or participation in the project. Participants will be provided with a URL, from which they will be able to subscribe to the listserv. Once subscribed, they will be able to post and receive messages, managed by a listserv moderator, who will be responsible for distribution to listserv members as appropriate. Participants will have the option to unsubscribe at any time.

### Handling of study interventions

To ensure intervention integrity, discrete components will follow written protocols and peer leaders will complete a standardized checklist for each session/encounter. Each IIP will be reviewed on a quarterly basis (every 3 months), at which time measures will be repeated and the participant will be invited to change and/or add options to their plan.

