### Description of the intervention

The intervention will be coordinated by an Intervention Coordinator, with assistance from local/MUSC Study Coordinators. The Intervention Coordinator will work with each participant in the intervention arm to create an IIP. Each IIP will include 1–4 options, including a mail-delivered arthritis kit, addition and access to a listserv, participation in a support group, and enrollment in local self-management program(s). Due to the nature of the IIP, the proposed intervention will inherently vary by participant. The total number of study visits will depend on group assignment and intervention participation. The entire study is over a period of 2 years. Location will vary depending upon the randomly assigned intervention. Locations range from a home setting to a set community meeting location.

For the past 5 years, South Carolina has been moving toward statewide infrastructure development for evidence based prevention programs (EBPPs). Under the combined leadership of the South Carolina Department of Health and Environmental Control (SCDHEC) and the South Carolina Lieutenant Governor’s Office Administration (SCLGOA), a number of EBPPs have been integrated into the program delivery of many aging services organizations and other local partner organizations. The Intervention Coordinator will assist interested participants with enrollment, and participants will be encouraged to take advantage of other programs after study completion.

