### Adherence assessment

In addition to quarterly review of their IIP, intervention participants will receive biweekly follow up calls to gauge their progress, comfort, adherence, and occurrence of any adverse events. In addition to enrollment in a local CDSMP, participants in the set menu control arm will receive monthly follow up calls to gauge their progress, comfort, adherence, and occurrence of any adverse events. Set menu controls will complete post-intervention follow-up evaluations bi-annually. Participants in the control arm will not receive follow-up calls, but will complete post-intervention follow-up evaluations on the same schedule as set menu controls. At their second post-intervention follow-up evaluation (after one year), set menu controls and controls will be invited to participate in the intervention activities of the program and have the opportunity to create their own IIP with the same options that were originally extended to intervention participants. From then, all participants will review their plan with the intervention coordinator on a quarterly basis, at which time measures will be repeated and each participant will be invited to change and/or add options to their plan. All participants will then receive monthly follow up calls to gauge their progress, comfort, adherence, and occurrence of any adverse events.

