### Outcomes assessments

Study assessments will be completed at baseline, 6 months, 12 months, 18 months, with a final evaluation at 24 months, for a total of five assessments. All patients who have agreed to participate will be mailed questionnaires for completion and compensation upon return, along with return postage and instructions for completing instruments. A randomly selected sub-sample (*n* = 50) of interested patients will be invited for assessment of urine catecholamine levels and urine collection instructions will be included in their mailed materials at baseline and 24 months/final evaluation. Mailed assessments will include: The Arthritis Self-Efficacy Scale, the Personal Health Questionnaire Depression Scale (PHQ-9), the Lupus Quality of Life Questionnaire (LUP-QOL), the Systemic Lupus Activity Questionnaire (SLAQ), and the Stanford Patient Education Research Center Questionnaires assessing medical outcomes such as hospital visits, illness intrusiveness, and use of stress management techniques.

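### The protocol gives two incompatible measurement schedules, one of which measures the intervention arm more often in the primary 12-month window; calls also differ by arm, so the set-menu contrast is not choice alone

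*Protocol article*

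**What the plan says.** Outcomes assessments applies one schedule to everyone. It covers all who agree to take part ("All patients who have agreed to participate will be mailed questionnaires for completion and compensation upon return"), and assessments are "completed at baseline, 6 months, 12 months, 18 months, with a final evaluation at 24 months, for a total of five assessments".

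Two other sections describe something different. Handling of study interventions states: "Each IIP will be reviewed on a quarterly basis (every 3 months), at which time measures will be repeated". In year 1 such plans exist in one arm only. Description of the intervention says "The Intervention Coordinator will work with each participant in the intervention arm to create an IIP", and the other two arms may build a plan only after one year (Concomitant interventions; Adherence assessment).

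For the comparators, Adherence assessment says "Set menu controls will complete post-intervention follow-up evaluations bi-annually" and puts the usual-care controls on the same timetable. The same section settles what the interval means: "At their second post-intervention follow-up evaluation (after one year), set menu controls and controls will be invited to participate". Two follow-up evaluations in a year is one every six months. From that point, the section has measures repeated quarterly for all participants.

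Adherence assessment also sets year-1 telephone contact. Intervention participants are called biweekly, "participants in the set menu control arm will receive monthly follow up calls", and controls are not called.

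The data analytic plan uses the first 12 months for the primary outcomes. It contrasts the intervention with control and with set menu, and describes the repeated factor only as pre, post and follow-up.

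**The concern.** The two schedules cannot both be followed, and they diverge between arms in the period that carries the primary comparison. If the quarterly schedule is used, the intervention arm answers the questionnaires at months 3 and 9 and the other arms do not. Apart from urinary catecholamines in a sub-sample, the outcomes are questionnaires answered by people who know which programme they were offered. Repeated completion can itself change how such questions are answered, so an imbalance in testing can produce, or hide, a difference between arms. If the month 3 and 9 values also entered the repeated-measures or imputation model, the arms would contribute different amounts of information.

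The calls raise a separate issue of interpretation. The Abstract and Discussion tie the expected benefit to participants choosing their own components. The set-menu arm is the comparator that could isolate choice, but it also differs in how often staff telephone.

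**Working it through.** No sample-size formula applies; the check is a count of occasions.

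**Step 1, the stated figure.** Outcomes assessments lists months 0, 6, 12, 18 and 24. That is 5 occasions, so the section's total agrees with its own list.

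**Step 2, the schedule in the other two sections.**
- Intervention arm, every 3 months throughout: 24/3 + 1 = 9 (0, 3, 6, 9, 12, 15, 18, 21, 24).
- Set-menu and control arms, every 6 months in year 1 and every 3 months afterwards: 3 (0, 6, 12) + 4 (15, 18, 21, 24) = 7.

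**Step 3, comparison, counting baseline.**

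| Source | Months 0–12 (intervention/set menu/control) | Months 0–24 |
|---|---|---|
| Outcomes assessments | 3/3/3 | 5/5/5 |
| Handling of study interventions with Adherence assessment | 5/3/3 | 9/7/7 |

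The intervention arm's 5 in the first year coincides with the stated total only by chance, because that total spans 24 months. Under the second schedule the post-baseline completions by month 12 are 4/2/2, and the unmatched occasions are months 3 and 9. After month 12 the arms share the same timetable, but months 15 and 21 still lie outside the list of five.

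**Step 4, calls in year 1.** Reading biweekly as every two weeks, the intervention arm has 52/2 = 26 calls, the set-menu arm 12 and the control arm 0. Read as twice a week, the first figure would be 52 × 2 = 104. On either reading the intervention arm is called more often than the set-menu arm.

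**Step 5, illustration of what a small non-specific shift could do.** The protocol gives no size for a testing or contact effect, so the shift *b* is an assumption. With 50 per arm and outcomes in SD units, an unadjusted two-arm comparison has SE = √(2/50) = 0.2. With no true effect of choice, the chance of a two-sided result at 0.05 is 1 − Φ(1.96 − b/0.2) + Φ(−1.96 − b/0.2):

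| Assumed b (SD) | Chance of a significant difference |
|---|---|
| 0 | 5.0% |
| 0.1 | 7.9% |
| 0.2 | 17.0% |
| 0.3 | 32.3% |

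These figures are the same whichever arm the shift favours. A shift against the intervention would instead tend to mask a real benefit.

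**The case against.** The strongest reply is that the section written to define outcome assessment is explicit. It gives times, a total and the population covered. The quarterly wording stands in sections on handling the intervention and on adherence, and does not name the measures. It could mean a shorter set, such as the practice diaries and self-rated practice frequency under Behavior change. If so, outcome occasions are 3/3/3 in the first year and the testing imbalance disappears. This possibility stands. However, no separate quarterly set is described, and Adherence assessment uses the same wording for all participants after year 1. A short set, if intended, has to be stated.

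It can also be said that bias is not demonstrated. That is right. The data analytic plan does not say that month 3 or 9 values enter the comparison, and imputation detail may properly sit in a fuller document.

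On contact, the trial can be read as comparing whole packages, with closer follow-up as part of the individualised one, and usual care naturally involves less contact. This is a fair reading. It supports the comparison as designed, but not a conclusion about self-selection by itself.

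Three stronger readings are tempting and not supported:
- **That the extra questionnaires are completed with the coordinator rather than by post.** The text gives only their timing, and Self-report measures allows mail or telephone by participant preference.
- **That the unequal calls contradict the five assessments.** They do not; calls are not assessments.
- **That call frequency must be equalised.** This is a debatable design choice, and under Safety monitoring the calls are also where adverse events are collected.

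**Conclusion.** The contradiction is established by the text and falls in the primary window: 5/3/3 against 3/3/3 occasions by month 12, and 9/7/7 against 5/5/5 by month 24. Under the quarterly wording no arm has the stated five.

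That this creates unequal testing of outcomes depends on reading the quarterly measures as the outcome questionnaires, which is likely but not certain. On that reading bias is possible in both contrasts, with size and direction unknown; the percentages above show sensitivity to an assumed shift and do not estimate one.

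The point on calls is independent of that reading. The intervention versus set-menu contrast estimates a-la-carte choice together with more frequent contact, and cannot be attributed to choice alone. The matter should be corrected, but a reader should not infer that the trial's comparison is already shown to be biased.

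**What to change.** 1. Reconcile Handling of study interventions, Adherence assessment and Outcomes assessments to one outcome schedule common to all arms.
2. For participants still in year 1, keep the quarterly review as a planning contact without the outcome questionnaires. If a shorter set was always intended there, name it.
3. Restrict the primary comparison to 0, 6 and 12 months in all arms. Exclude any month 3 and 9 values already collected from both the primary model and the imputation model.
4. State that the intervention versus set-menu contrast estimates a-la-carte choice plus more frequent contact, and limit the conclusion to that.

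The cost is mainly wording. The month 3 and 9 trajectories are lost, but they exist in one arm only and have no comparator; the conclusion becomes slightly narrower. Trial status reports 153 randomised and 30 with all assessments complete, so item 2 cannot help those already past month 12. Items 3 and 4 still can. Excluding the extra values equalises the data analysed but does not undo extra testing that has already taken place; where it has, the report should say so.

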### Concomitant interventions

During the first intervention year, intervention arm participants will have the option of participating in a mail-delivered arthritis kit, addition and access to a listserv, participation in a support group, and/or enrollment in local self-management program(s). After one year, set menu controls and controls will be invited to participate in the same options that were originally extended to intervention participants. During the first intervention year, set menu control arm participants will not have the option of participating in a mail-delivered arthritis kit, addition and access to a listserv, or participation in a support group. Control arm participants will not have the option of participating in any of the four offered intervention modalities. None of the offered intervention modes are required.

### Adherence assessment

In addition to quarterly review of their IIP, intervention participants will receive biweekly follow up calls to gauge their progress, comfort, adherence, and occurrence of any adverse events. In addition to enrollment in a local CDSMP, participants in the set menu control arm will receive monthly follow up calls to gauge their progress, comfort, adherence, and occurrence of any adverse events. Set menu controls will complete post-intervention follow-up evaluations bi-annually. Participants in the control arm will not receive follow-up calls, but will complete post-intervention follow-up evaluations on the same schedule as set menu controls. At their second post-intervention follow-up evaluation (after one year), set menu controls and controls will be invited to participate in the intervention activities of the program and have the opportunity to create their own IIP with the same options that were originally extended to intervention participants. From then, all participants will review their plan with the intervention coordinator on a quarterly basis, at which time measures will be repeated and each participant will be invited to change and/or add options to their plan. All participants will then receive monthly follow up calls to gauge their progress, comfort, adherence, and occurrence of any adverse events.

### Outcomes assessments

Study assessments will be completed at baseline, 6 months, 12 months, 18 months, with a final evaluation at 24 months, for a total of five assessments. All patients who have agreed to participate will be mailed questionnaires for completion and compensation upon return, along with return postage and instructions for completing instruments. A randomly selected sub-sample (*n* = 50) of interested patients will be invited for assessment of urine catecholamine levels and urine collection instructions will be included in their mailed materials at baseline and 24 months/final evaluation. Mailed assessments will include: The Arthritis Self-Efficacy Scale, the Personal Health Questionnaire Depression Scale (PHQ-9), the Lupus Quality of Life Questionnaire (LUP-QOL), the Systemic Lupus Activity Questionnaire (SLAQ), and the Stanford Patient Education Research Center Questionnaires assessing medical outcomes such as hospital visits, illness intrusiveness, and use of stress management techniques.

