### Primary outcome

We expect the proposed study to demonstrate that a unique intervention strategy can reduce disease activity and damage, as well as perceived and biological indicators of stress, while improving quality of life indicators in African-American lupus patients. This will result in changes (a) health behaviors (use of stress management techniques), (b) health status (quality of life, depression, perceived psychosocial stress, and disease activity), (c) health care utilization (hospitalizations, emergency room visits, and communication with physicians) and (d) biological markers (urinary catecholamines).

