### Sample size and power

There will be three study arms in the proposed study; (1) intervention, (2) set menu control, and (3) control. Due to the potential similarity in each arm, a cluster-random trial will be considered, which takes into account between-cluster variation [94]. Relevant intervention literature shows effect sizes varying from 30-80 % [26, 29, 31, 39, 42, 45, 46, 49–51], which will be adequate for the proposed sample size design. The study will evaluate the difference in disease indices, quality of life and perceived and biological indicators of stress between the intervention and control groups, as well as within each group according to individual levels of intervention participation. Therefore, estimated sample sizes are displayed in Table 1 under a variety of effect sizes and drop-out levels in order to obtain a 0.95 significance level and 0.8 power of study. Our target recruitment level will be 150 participants according to an 80 % power level, in an effort to capture smaller effect sizes. This will correspond to an approximate 45 % response rate (*N* = 336), which is well within response and participation in other studies among the MUSC lupus cohort. Based on these results there is good to adequate power for most analyses to make the proposed project feasible.

**Table 1 Tab1:** Estimated sample size calculations

Estimated sample sizes				
Effect size	0.4	0.6	0.7	0.8
Sample size per arm (No drop out)	51	23	18	14
Sample size per arm (10 % drop out)	86	38	28	22
Sample size per arm (15 % drop out)	91	41	30	23

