### Data analytic plan

#### Quantitative data analysis

Data will be entered immediately after specified collection points into an Excel worksheet that will be built upon after each collection point and imported into SAS for data manipulation. To minimize risks to confidentiality, all data will be de-identified by assigning a numeric code to each participant and labeling all materials corresponding to that participant with their unique identifier. Additionally, data files that include personal identifiers will be stored separately from signed consent forms in locked file cabinets that only the Principal Investigator will have access to. The basic experimental design and corresponding data analyses will represent a one-between subjects (intervention versus control and intervention versus set menu control) and one-within or repeated factor (pre, post, and follow up assessments) crossed factorial design, with multiple dependent outcome measures (disease activity and damage, perceived and biological indicators of stress, quality of life, and urine catecholamines). The multivariate (multiple qualitatively distinct measures at multiple times) approaches to repeated measures [95, 96], based on the general linear model or general linear mixed model, will be used to test for pre-post-follow up changes between the intervention group and the control groups, as well as for exploratory correlations with urine catecholamines. These approaches provide better description of longitudinal patterns for each dependent variable and they are easier to successfully implement and generally more powerful than the use of covariant models when multiple outcome measures are considered simultaneously [96]. *P* < 0.05 will be used to indicate statistical significance. The data from all randomized participants will be analyzed. Multiple imputations will be used to estimate missing data from dropouts and those participants who do not complete follow up evaluations. We will evaluate the first 12 months to address primary outcomes and exploratory analyses will be conducted after 12 months once participants are given the option to cross over. Basic descriptive statistics such as means, ranges, and standard deviations will be calculated and tabulated for quantitative data using SAS (SAS Institute, Cary, North Carolina). Project-specific frequencies and percentages will be presented as a recruitment diagram according to CONSORT guidelines.

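### Urinary catecholamines are listed as a primary outcome and fall under the 80% power statement, but are measured in only 50 patients, which does not give that power between arms

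*Protocol article*

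**What the plan says.** Four places in the protocol article bear on this outcome.

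- *Primary outcome* gives four domains, the last being "d) biological markers (urinary catecholamines".
- *Outcomes assessments* limits the measurement to a random draw of 50: this number "of interested patients will be invited for assessment of urine catecholamine levels". On timing, the same section says that "urine collection instructions will be included in their mailed materials at baseline and 24 months/final evaluation".
- *Sample size and power* sets the scope of the calculation: "The study will evaluate the difference in disease indices, quality of life and perceived and biological indicators of stress between the intervention and control groups". It goes straight on to Table 1, calculated "in order to obtain a 0.95 significance level and 0.8 power of study", and sets the target at 150 so as to reach smaller effects. It concludes: "Based on these results there is good to adequate power for most analyses to make the proposed project feasible". It neither exempts catecholamines nor gives a calculation for the 50.
- *Quantitative data analysis* names urine catecholamines among the dependent outcomes, and then describes the multivariate models as serving tests of change between groups "as well as for exploratory correlations with urine catecholamines". It assigns primary outcomes to the first 12 months and treats analyses after that as exploratory.

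**The concern.** A reader who puts the primary-outcome and sample-size sections together will take the catecholamine comparison to have 80% power at the effects in Table 1. It rests on one third of the patients behind that statement. A null result could then be reported as evidence against a biological effect when the comparison had little chance of showing a modest one. The status of the outcome is also unsettled, because one section calls it primary and the analysis rule places its only follow-up value in the exploratory period.

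**Working it through.** **Inputs.** From the article: sub-sample 50; three arms; target 150, so 50 per arm; power 0.8; significance threshold 0.05 (sidedness not stated); Table 1 effects 0.4, 0.6, 0.7 and 0.8, read as standardised differences. Assumed: equal split, 50/3 = 16.7, about 17 per arm; two-sided test.

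**Table 1 first.** It reproduces to within one patient, but only with two different formulas.

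- No-drop-out row (51/23/18/14): a one-sample or paired t-test, two-sided 5%, gives 51.0/23.8/18.0/14.3.
- Drop-out rows: a two-sample t-test, one-sided 5%, gives 78.0/35.0/25.9/20.0. Divided by 0.90 or 0.85 and rounded down, this is 86/38/28/22 and 91/41/30/23, as printed.
- A two-sided two-sample test with no drop-out needs about 99/45/33/26 per arm.

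**Against Table 1 as printed.** Seventeen per arm is below 11 of the 12 entries. The exception is effect 0.8 with no drop-out (14), which matches the paired formula and not a between-arm one.

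**Between-arm power for catecholamines.** Power is the probability that a noncentral t with 2n − 2 degrees of freedom and noncentrality d·√(n/2) exceeds the two-sided 5% critical value. With a baseline covariate of correlation r, d is replaced by d/√(1 − r²) and one degree of freedom is lost.

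| Per arm | d = 0.4 | 0.6 | 0.7 | 0.8 | Detectable at 80% |
|---|---|---|---|---|---|
| 17, unadjusted | 0.20 | 0.40 | 0.51 | 0.62 | 0.99 SD |
| 16.7, unadjusted | 0.20 | 0.39 | 0.50 | 0.61 | 1.00 SD |
| 15 (10% loss), unadjusted | 0.18 | 0.36 | 0.46 | 0.56 | 1.06 SD |
| 16.7, r = 0.5 assumed | 0.25 | 0.49 | 0.62 | 0.73 | 0.87 SD |
| 16.7, r = 0.7 assumed | 0.35 | 0.65 | 0.78 | 0.88 | 0.72 SD |
| 50, unadjusted, for comparison | 0.51 | 0.84 | 0.93 | 0.98 | 0.57 SD |

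Quick check by the normal approximation: (1.96 + 0.84)·√(2/17) = 0.96 SD. The t-distribution raises this to 0.99.

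**Sensitivity to sidedness and split.**

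- One-sided 5% at 17 per arm: power 0.31 at 0.4 and 0.74 at 0.8.
- If 50 of 150 are drawn without regard to arm, the count in an arm has SD 2.7 (95% range 11 to 22). A comparison of 11 with 22 is worth 2·11·22/33 = 14.7 per arm.
- At the other extreme, if all 50 fell in the two arms compared (25 each), power would be 0.28 at 0.4 and 0.79 at 0.8.

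**Timing, set side by side.** Primary outcomes: first 12 months. Urine: baseline and 24 months. Both control arms are offered the intervention options at one year (*Concomitant interventions*, *Adherence assessment*). So no post-baseline urine value falls in the primary window, and the one that exists follows the cross-over offer.

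**The case against.** The best defence is that the article already takes these data out of the primary analysis. By its own rule, analyses after 12 months are exploratory, and follow-up urine exists only at 24 months. This stands in part. A reader might infer that a chance positive catecholamine result would count as a primary success; the analysis rule does not support that. What it leaves is a conflict with the primary-outcome section, where catecholamines are still listed. The word exploratory is attached only to correlations, and the same section names catecholamines as a dependent outcome.

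Second, power is claimed for most analyses, not all. That also stands: no statement is specific to catecholamines, and a reader who infers an explicit 80% promise for them goes too far. But the hedge names no exception, and biological indicators are expressly within the comparisons.

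Third, the planned models can use the baseline sample, so the unadjusted figures are pessimistic. This is fair. With r = 0.7 an effect of 0.8 reaches 88% power, so it is too strong to say that only very large effects can be detected. The correlation is not given, and at 0.4 power stays at or below about 35% for either assumed value.

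Fourth, the section also covers change within groups, for which the paired entry at 0.7 (18) nearly fits 17 per arm. That does not help the comparison between arms.

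Finally, the article does not imply heavy refusal: the 50 may be drawn from patients who have already shown interest. No figure here depends on a low uptake.

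**Conclusion.** The concern holds in a limited form. For urinary catecholamines, the design does not deliver 80% power between arms across Table 1's effects. Unadjusted two-sided power is about 20% at 0.4 and 62% at 0.8, and the detectable effect is about 1.0 SD, or 0.87 to 0.72 SD with baseline adjustment at r = 0.5 to 0.7. The smaller effects that the target of 150 is meant to reach stay far below 80%. These figures assume an equal split, both samples returned by all 50 and, for the adjusted values, the stated correlations. None of them allows for the offer of the options to the control arms at one year. The primary label also conflicts with the analysis section.

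A reader might infer that the whole trial lacks its stated power for this reason. The point does not reach that far, because the questionnaire outcomes are mailed to all participants. This should be fixed, but it does not threaten the main comparisons.

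**What to change.** 1. Reconcile *Primary outcome*, *Sample size and power* and *Quantitative data analysis* by labelling urinary catecholamines exploratory throughout. Record that the change was made after randomisation, since *Trial status* reports 153 randomised and 30 with all assessments complete.
2. State in *Sample size and power* that Table 1 and the 80% figure do not apply to catecholamines.
3. Give the expected precision for the 50-patient sub-sample with its assumptions: split by arm, number returning both samples, and any baseline adjustment with its correlation. Add that the 24-month contrast follows the offer of the options to both control arms, so a detectable effect for a standard parallel-arm comparison does not fully describe it.

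Stratifying randomisation by sub-sample membership or replacing patients who decline is no longer practical, because enrolment has passed its target.

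The cost is a change of wording and a documented mid-trial reclassification of one listed outcome, with a more modest claim for the biomarker. No further patients or assays are needed.

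### Urinary catecholamines are a primary outcome judged over the first 12 months, but the only follow-up urine sample is at 24 months, a year after both control arms may cross over

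*Protocol article*

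**What the plan says.** All statements are in the protocol article.

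- *Primary outcome*: the last of four outcome domains is given as "d) biological markers (urinary catecholamines".
- *Quantitative data analysis*: the dependent measures of the between-arm repeated-measures design are "disease activity and damage, perceived and biological indicators of stress, quality of life, and urine catecholamines". On timing, the section says "We will evaluate the first 12 months to address primary outcomes and exploratory analyses will be conducted after 12 months"; the reason it gives is the cross-over option.
- *Outcomes assessments*: for the questionnaires, "Study assessments will be completed at baseline, 6 months, 12 months, 18 months, with a final evaluation at 24 months". For urine, a random sub-sample of 50 is drawn from patients who express interest, and the dates are fixed as follows: "urine collection instructions will be included in their mailed materials at baseline and 24 months/final evaluation".
- *Concomitant interventions*: "After one year, set menu controls and controls will be invited to participate in the same options that were originally extended to intervention participants". The same section says that no mode is compulsory.
- *Adherence assessment* places this invitation at a visit: "At their second post-intervention follow-up evaluation (after one year), set menu controls and controls will be invited to participate".

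**The concern.** A primary outcome needs at least one follow-up measurement inside the period in which primary outcomes are judged. Catecholamines have none: their single follow-up value comes when every arm has been offered the full set of options for at least a year. An analysis plan cannot repair this, because it cannot analyse a sample that was not collected.

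What is at stake is the claim, made in the abstract, the study aims and the primary outcome, that the programme reduces biological indicators of stress. On this schedule the claim cannot be tested against people who have not been offered the programme. A null result at 24 months could mean that there is no effect, that the control arms caught up, or that the sub-sample was too small.

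**Working it through.** **Timing.** The dates, side by side:

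| Item | Month | Section |
|---|---|---|
| Urine collection | 0, 24 | Outcomes assessments |
| Questionnaires | 0, 6, 12, 18, 24 | Outcomes assessments |
| Primary evaluation window | 0 to 12 | Quantitative data analysis |
| Both control arms invited to cross over | 12 | Concomitant interventions; Adherence assessment |

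The number of post-baseline urine samples in months 0 to 12 is 0. The only follow-up sample comes 24 − 12 = 12 months after the window closes and the invitation is made. At that point the intervention arm has had the options on offer for 24 months and the control arms for 12. The 24-month contrast is therefore an immediate against a delayed offer.

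Two other passages might seem to supply an earlier sample, but neither does. *Handling of study interventions* and *Adherence assessment* say that measures are repeated quarterly, but that is general wording, and the specific statement for urine gives two dates. The extra collection in *Neuroendocrine response to stress* is an immediate repeat to assess variability.

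**Size of the sub-sample.** The plan gives no power figure for catecholamines, so there is none to reproduce. Inputs:

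- 50 participants in the sub-sample (*Outcomes assessments*) and three arms. Assuming an even spread, n = 50/3 = 16.7 per arm.
- Significance level 0.05 (*Quantitative data analysis*); two-sided is assumed, as sidedness is not stated.
- Power 0.8 and effect sizes 0.4, 0.6, 0.7 and 0.8 SD (*Sample size and power*, Table 1).
- No drop-out is assumed.

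Detectable difference at 80% power = (1.960 + 0.842) × √(2/n) = 2.802 × √(2/16.7) = 0.97 SD. The t-test equivalent is 1.00 SD (0.99 SD with 17 per arm).

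Power = Φ(d × √(n/2) − 1.960), with √(16.7/2) = 2.887:

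| d (SD) | d × 2.887 − 1.960 | Power, normal | Power, t-test |
|---|---|---|---|
| 0.4 | −0.805 | 21% | 20% |
| 0.6 | −0.228 | 41% | 39% |
| 0.7 | 0.061 | 52% | 50% |
| 0.8 | 0.349 | 64% | 61% |

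These values assume that the full contrast is still present. Uptake after cross-over is not given, so the fraction of the contrast left at 24 months is an assumption:

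| Fraction left | Power at 0.4 SD | Power at 0.8 SD |
|---|---|---|
| 1 | 21% | 64% |
| 0.75 | 14% | 41% |
| 0.5 | 8% | 21% |

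**The case against.** The strongest reply is that the document already treats catecholamines as partly exploratory. *Quantitative data analysis* mentions exploratory correlations with them. *Secondary outcome* relates neuroendocrine response to participation, and *Sample size and power* plans analyses within each group by level of participation. Baseline and 24-month samples can serve those aims, so the late sample has a use. That stands, and it suggests that the defect is largely one of labelling. It does not remove the conflict, because the same document also calls catecholamines primary and lists them as a dependent measure of the between-arm model.

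It is also fair to say that only one of four domains is affected. The other three are measured by questionnaire, scheduled for all participants at 6 and 12 months.

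Two stronger readings are tempting but unsupported:

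- A reader might infer that no randomised comparison of catecholamines exists. One does, at 24 months, by arm as randomised. Under the plan's own rule it is exploratory. Cross-over is an invitation only, so the dilution could be small or large.
- A reader might fault the sub-sample for being drawn without regard to arm. The article says only that it is randomly selected, and a condensed article may leave the method to the full protocol. By *Randomization*, baseline assessments come back before arms are assigned, so arm was not known when baseline urine was requested. Nor could places now be filled by arm: *Trial status* reports 153 randomised against a target of 150, and anyone added now would have no pre-randomisation urine sample.

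**Conclusion.** The point holds as a contradiction within the protocol article. The primary status of catecholamines, the 12-month primary window and the urine dates cannot all be followed. There are 0 post-baseline samples in the primary window, and no comparison with unexposed controls is possible before cross-over. This follows from the stated dates alone.

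The power figures are secondary and rest on assumptions: an even spread of 50 over three arms, a two-sided test and no drop-out. On those terms a pairwise comparison falls short of 80% power at every effect size in Table 1. The documents do not show how far cross-over weakens the 24-month contrast; a shift toward no difference requires that controls take up the offer and respond to it.

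**What to change.** 1. *Primary outcome*: move urinary catecholamines from primary to exploratory, and leave the effect on biological indicators of stress out of the primary conclusion.
2. *Quantitative data analysis*: take catecholamines out of the dependent measures of the primary between-arm model and keep them as exploratory.
3. *Outcomes assessments*: state that the 24-month urine comparison between arms is an immediate versus a delayed offer, so that the three sections agree.

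This costs a text amendment and needs no new data. What is given up is a primary claim that the schedule cannot support.

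Optionally, collect urine with the existing 12-month mailing, before the cross-over invitation, from sub-sample members who have not yet reached it, and report the result as exploratory. This would restore a pre-cross-over contrast for those people only. *Trial status* reports that 30 participants have completed all assessments, and the number of others past month 12 is not given. If this collection replaces the 24-month one, time points are mixed and each has fewer than the already small 17 or so per arm. If it is added, the cost is one further 24-hour collection per person. Neither version gives adequate power.
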